### Statistical analysis

#### Sample size

The two primary outcomes of our study are the incidence of pain and the intensity of pain using the VAS score. In accordance with Tsai et al. [20], we have measured pain intensity using the preliminary data of the 24-h and 48-h pain scores. Post-laparoscopic pain is most common and evident in the first 48 h after surgery, after that the pain declines. That is why we have chosen to look at the 48-h pain score. Furthermore, we have assumed a reduction in the incidence of pain from 80% to 50% using this combination treatment compared to standard treatment [7, 24]. A dropout rate of 20% is anticipated because of loss to follow-up or incomplete questionnaires. We use Fisher’s exact test to test for differences in the proportion. To do so, we need to include at least 126 patients (63 women in each study arm) to obtain a power of 85% when testing with an alpha of 5%.

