#### Data analysis

Data will be analyzed according to the intention–to-treat principle. Statistical analysis will be performed using the software Statistical Package for the Social Sciences 22.

Categorical variables will be described as frequencies and percentages. Continuous variables will be described in terms of means with standard deviation if normally distributed, and otherwise as a median with an interquartile range (IQR). Significance will be tested two sided with an α-level of 0.05. Patients will be classified as either having pain or not having pain using the questionnaires the patients fill in after surgery. To compare the incidence of pain between the intervention and control groups, the Pearson’s Chi-squared statistic will be used. For those patients experiencing pain, the average pain scores between groups will be compared. T-tests for pain scores will be used when the scores are normally distributed.

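### Pain intensity, a primary outcome, is compared only among women who have pain, so the comparison is not between randomised groups and can make an effective treatment look harmful

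*Protocol article*

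**What the plan says.** The Sample size section of the protocol article names the primary outcomes: "The two primary outcomes of our study are the incidence of pain and the intensity of pain using the VAS score". The Measurement and follow-up section agrees and lists three sites and three time points.

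The Data analysis section first forms two classes: "Patients will be classified as either having pain or not having pain using the questionnaires the patients fill in after surgery". Incidence is then compared with Pearson's chi-squared test. For intensity, the only comparison stated is: "For those patients experiencing pain, the average pain scores between groups will be compared". The test is given next: "T-tests for pain scores will be used when the scores are normally distributed". No comparison of intensity in all randomised women appears anywhere in the article.

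The same section opens with this principle: "Data will be analyzed according to the intention–to-treat principle". The sample-size section sets out the expected effect on incidence: "we have assumed a reduction in the incidence of pain from 80% to 50" percent.

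**The concern.** Whether a woman has pain is an outcome, measured after allocation. If treatment changes it, as the design assumes, the women with pain in one arm are not the counterparts of the women with pain in the other. Randomisation then no longer protects the comparison, and a difference in mean VAS mixes any effect on severity with the difference in who was selected.

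The direction matters most. Suppose the intervention clears mild pain and leaves severe pain alone. Women with mild pain then leave the intervention arm's analysis but stay in the control arm's, and the remaining intervention mean goes up. A treatment that harms nobody and helps some could give a significant result against itself on a primary outcome.

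This is not detail left for an analysis plan to supply. The article states a restricted comparison and attaches it to a primary outcome.

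**Working it through.** **Inputs from the article.** Pain incidence 80% (control) and 50% (intervention); two-sided alpha 0.05; power 85%; dropout 20%; planned 63 per arm; amended target 100 per arm (Results section).

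**Inputs assumed.** The article gives no VAS mean or SD. Two models were used, both on a 0-10 scale with pain-free = 0.
- Model 1: latent pain is normal with SD 2.5, and 80% of controls lie above 0.
- Model 2: control women with pain have mean 4 and SD 2.

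**1. The plan's own sample size.** Fisher's exact test at 80% versus 50% has power 0.842 with 49 per arm and 0.853 with 50. Allowing for dropout, 50 / (1 − 0.20) = 62.5, so 63 per arm and 126 in total. The stated size reproduces, and it covers incidence only.

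**2. Who enters the intensity comparison (no VAS assumption needed).**
- Per 100 per arm: 80 control versus 50 intervention. Excluded: 20 + 50 = 70 of 200, or 35%, with 50/20 = 2.5 times as many from the intervention arm.
- With 50 evaluable per arm (63 × 0.80 ≈ 50): 40 versus 25.
- With 80 evaluable per arm (100 × 0.80): 64 versus 40.

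**3. A hand example (scores assumed).** Of 100 control women, 20 score 0, 30 score 2 and 50 score 5. Treatment clears the 30 mild cases and changes nobody else.
- Women with pain: control (60 + 250)/80 = 3.875; intervention 250/50 = 5.00; difference +1.125, apparent harm.
- All women: 310/100 = 3.10 versus 250/100 = 2.50; difference −0.60, benefit.

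**4. Model 1, means.** Incidence of 80% needs a latent mean of 0.84 × 2.5 = 2.10. Control mean among women with pain = 2.10 + 2.5 × φ(0.84)/0.80 = 2.979; over all women, 0.80 × 2.979 = 2.383. The intervention arm reaches 50% incidence in one of three ways:

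| Mechanism | Intervention, with pain | Intervention, all | Difference, with pain | Difference, all |
|---|---|---|---|---|
| (a) mildest pain abolished | 2.10 + 2.5 × 0.798 = 4.10 | 0.5 × 4.10 = 2.05 | +1.12 | −0.33 |
| (b) uniform downward shift | 2.5 × 0.798 = 1.995 | 0.5 × 1.995 = 0.997 | −0.98 | −1.39 |
| (c) pain abolished at random | 2.979 | 0.5 × 2.979 = 1.490 | 0.00 | −0.89 |

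**5. Model 1, simulated tests.**
- (a) The t-test among women with pain is significant for harm in about 69% of trials at 50 evaluable per arm and 88% at 80. The rank test in all women finds benefit in 27% and 40%.
- (b) The t-test among women with pain has about 59% power at 50 per arm and 79% at 80. Tests in all women have 97-98% at 50.
- (c) The t-test among women with pain finds nothing beyond its nominal error rate. The rank test in all women has 77% power at 50 per arm.

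**6. Model 2, 100 per arm before dropout.**

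| Mechanism | Difference, with pain | Difference, all | t-test among women with pain significant for harm |
|---|---|---|---|
| mildest cleared, rest unchanged | +1.17 | −0.64 | 97% |
| mildest cleared, rest fall by 0.5 | +0.70 | −0.87 | 59% |
| mildest cleared, rest fall by 1 | +0.20 | −1.11 | 8% |
| abolished at random | 0.00 | −1.21 | 2.5% (nominal) |
| uniform shift | −2.18 | −2.29 | 0% |

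At 50 per arm the first two rows give 78% and 30%.

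**The case against.** The strongest reply is that incidence and severity among sufferers form a two-part description. Women made pain-free are counted under incidence, which is tested in all women and drives the sample size, so their benefit is not lost to the trial. That is true for the trial as a whole. It does not rescue intensity as a primary outcome in its own right, because the article gives no joint test or joint reading of the two parts.

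Several narrower points stand:
- Reversal is not inevitable. It needs treatment to remove mainly mild pain while doing little for the rest. Under random abolition the difference among women with pain is zero, which correctly describes women who still hurt. Under a uniform shift the sign is right. Nothing in the article says which mechanism is likely.
- In mechanism (a) the repaired analysis has low power too: 27% by rank test and about 12% by t-test at 50 per arm. It removes the misleading sign but would often miss that effect.
- The intention-to-treat sentence can be read as meaning only that women are analysed in their allocated arm, which the restricted comparison still does. The conflict with that sentence is secondary to the selection on outcome.
- The 80% and 50% are not tied to a site or time, and the article does not say whether having pain means any pain or pain at that site and time. The share excluded from a given comparison could be smaller or larger than shown.

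**Conclusion.** The concern holds. The plan fixes the comparison of a primary outcome to a subset defined by the other primary outcome, which it expects treatment to change. By its own rates it leaves out 20% of controls and 50% of the intervention arm. That imbalance comes from the document alone.

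The consequences depend on assumed VAS distributions and on the mechanism. The result may be a significant finding in the wrong direction (about 69% of trials at 50 evaluable per arm and 88% at 80, if the mildest pain is abolished under Model 1), no visible intensity effect (random abolition), or a loss of power (59% against 97-98% at 50 per arm, uniform shift under Model 1). In every mechanism tried, the contrast among women with pain differs from the difference over all women. It should be corrected before intensity is analysed by arm.

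**What to change.** Replace the sentence on intensity in the Data analysis section with wording to this effect:

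> Pain intensity will be compared between the randomised groups in all women with a VAS score at the site and time concerned, a woman without pain counting as 0, by a van Elteren rank test stratified by hospital. Mean scores among women with pain will be reported by arm as description only, without a test.

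The rank test suits data in which 20% to 50% of scores may be zero, and hospital is already the randomisation stratum. A mixed model over 8, 24 and 48 h with treatment, time, their interaction and hospital could be given as support. As the primary analysis it is less suitable, because normal errors fit poorly with so many zeros. Say also that having pain is judged at the same site and time as the score.

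The cost is one or two sentences in the analysis section. No new data and no extra patients are required.

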### Measurement and follow-up

Primary outcomes are the incidence and intensity of post-laparoscopic pain in shoulder, upper abdomen and at the operating site at 8, 24 and 48 h after surgery, which are measured using the Visual Analogue Scale (VAS). Secondary outcomes are postoperative use of analgesics, nausea, vomiting and pulmonary complications. We will record patient characteristics (age, height, weight, body mass index (BMI)) and operative details (type of surgery, ASA-classification, duration of surgery, estimated blood loss, total volume of gas used, amount of normal saline left intraperitoneal, and postoperative hospital stay).

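### Pain intensity, measured three times in the same women, is tested only by t-test among women with pain; one declared contrast per site from a model on all randomised women would be better

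*Protocol article*

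**What the plan says.** Under Measurement and follow-up, the protocol article states: "Primary outcomes are the incidence and intensity of post-laparoscopic pain in shoulder, upper abdomen and at the operating site at 8, 24 and 48 h". The abstract and the Objective list the same sites and times.

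Under Sample size it names two primary outcomes ("The two primary outcomes of our study are the incidence of pain and the intensity of pain using the VAS score") and, after noting that pain is most evident in the first 48 h, adds: "That is why we have chosen to look at the 48-h pain score". It also expects loss of data: "A dropout rate of 20% is anticipated because of loss to follow-up or incomplete questionnaires".

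Under Data analysis it adopts the intention-to-treat principle and a two-sided 5% level. It then describes the intensity comparison in two sentences: "For those patients experiencing pain, the average pain scores between groups will be compared", and "T-tests for pain scores will be used when the scores are normally distributed". No other test for intensity is named.

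**The concern.** Three problems meet in those two sentences on intensity.

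1. **Time point.** A two-sample t-test takes one value per woman. Three times per site are called primary, so the natural reading is three tests per site for one question, each at 5%. The sample size section points to 48 h alone. The sections do not agree on what the intensity test is.
2. **Missing scores.** A woman without a 48-h score contributes nothing to a 48-h t-test, although her 8-h and 24-h scores carry information about it. The plan itself expects incomplete questionnaires.
3. **Analysis set.** Intensity is compared only in women with pain. Having pain is itself an outcome that the treatment is expected to change, so the two groups compared are no longer those that randomisation made alike. This conflicts with the intention-to-treat principle stated in the same section.

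At stake is whether the trial gives one interpretable, randomisation-based answer on intensity per site.

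**Working it through.** **Inputs from the protocol article**
- Pain incidence 80% control, 50% intervention; 20% loss; 63 per arm; 85% power; Fisher's exact test (Sample size).
- 100 women per arm after the amendment (Results).
- Three sites, three times (Measurement and follow-up); two-sided 0.05 (Data analysis).

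**Assumptions, because the article gives no figure**
- Within-woman correlation ρ between times: 0.3, 0.5 or 0.7, equal for all pairs, with equal variances.
- Intensity effect of 0.4 SD.
- The 20% loss falls only on the 48-h score. This is the case most favourable to a model.

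**The plan's own figure.** Exact enumeration of the two-sided Fisher test for 80% against 50% gives power 0.842 with 49 per arm and 0.853 with 50. Then 50/0.8 = 62.5, rounded up to 63 per arm, 126 in total. The stated size reproduces. It rests on incidence alone, so nothing below changes it.

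**False-positive risk if each time is tested.** For three independent tests, 1 − 0.95³ = 0.143. Simulating correlated test statistics gives about 0.135, 0.125 and 0.11 at ρ = 0.3, 0.5 and 0.7.

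**Women entering the comparison.** Evaluable per arm: 100 × 0.8 = 80. With pain: 80 × 0.80 = 64 control and 80 × 0.50 = 40 intervention. At 63 per arm without loss the figures are about 50 and 32. The planned rates are not given by site and time, so these counts are illustrative. At 0.4 SD, t-test power is 71% with 80 against 80, but about 50% with 64 against 40.

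**Gain for the 48-h contrast.** The share of 48-h variance explained by the other two scores is R² = 2ρ²/(1 + ρ). The contrast variance, relative to full data, is 1/0.8 = 1.25 for the t-test and R² + (1 − R²)/0.8 for the model. Power is for 100 randomised per arm.

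| ρ | R² | Model variance | Ratio to 1.25 | Power at 0.4 SD |
|---|---|---|---|---|
| 0.3 | 0.138 | 1.215 | 0.97 | 72% |
| 0.5 | 0.333 | 1.167 | 0.93 | 74% |
| 0.7 | 0.576 | 1.106 | 0.88 | 76% |

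The t-test has 71%, so variance falls by about 3 to 12%. Both analyses here use all women, not only those with pain.

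**Gain for a time-averaged contrast.** The variance of the mean of three scores relative to one is (1 + 2ρ)/3 = 0.53, 0.67 and 0.80. With 80 complete women per arm, power depends on how many of the three times carry the 0.4 SD effect:

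| Effect present at | ρ = 0.3 | ρ = 0.5 | ρ = 0.7 |
|---|---|---|---|
| all three times | 93% | 87% | 80% |
| two times | 63% | 54% | 47% |
| one time | 21% | 18% | 16% |

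The single-time t-test has 71% at a time when the effect exists.

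**The case against.** **The article never says that each time is tested separately.** This stands. The wording on average pain scores, together with the sentence choosing 48 h, leaves room for a single test. If 48 h is the only confirmatory time, time adds no tests and the 14.3% falls away. But that reading conflicts with the abstract, the Objective and Measurement and follow-up, so the sections need reconciling in any case.

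**The model gives little.** For a like-for-like 48-h contrast this is right. A reader might infer from the time-averaged figures that a mixed model lifts power from 71% to 80–93%. The documents do not support that. The rise comes from asking a time-averaged question under a constant effect. With complete data, a plain t-test on each woman's mean score would have the same variance. Nothing in the article says that the effect is constant over time.

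**The loss of women is smaller than it sounds.** Also right. A t-test loses a woman only at the time she has no score. The 20% includes loss to follow-up, and a woman with no score at all adds nothing to a model either.

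**A t-test at one time is valid, and modelling detail belongs in an analysis plan that is not shown.** On all randomised women with a score, and apart from missing data, a t-test would indeed be a valid comparison. But the article restricts it to women with pain. That restriction and the choice of test are stated, not left out.

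**Conclusion.** The concern holds in a limited form. The article is inconsistent on the time point for intensity. Its stated test does not use the repeated scores, and its analysis set departs from its own intention-to-treat principle. The last is the most serious: about 64 against 40 women would be compared out of 80 evaluable per arm, selected on an outcome that the treatment is expected to change.

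The multiplicity figure (11 to 14.3% per site) applies only if all three times are tested. The precision gain at 48 h is small (variance down 3 to 12%; power 71% to 72–76%). It depends on the assumed correlations, the assumed 0.4 SD effect and loss confined to 48 h. A time-averaged contrast gains more only if the effect is similar at all three times.

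A reader might also infer that one model per site settles multiplicity. It does not: a single contrast must still be declared, and the three sites and two primary outcomes remain.

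**What to change.** 1. Reconcile Measurement and follow-up with Sample size on the time point, and declare one intensity contrast per site: either the 48-h difference or the difference averaged over the three times. Prefer the average only if a similar effect at all times is expected.
2. Estimate it from one linear mixed model per site on all randomised women with at least one score, with VAS = 0 when no pain is reported. Include arm, time, arm-by-time and hospital (the stratification factor), with an unstructured covariance over the three times. Use robust or bootstrap standard errors, because the planned rates imply zeros for about 20% of control and 50% of intervention women.
3. Report the other times as supportive, and intensity among women with pain as descriptive.
4. State separately how multiplicity across the three sites and the two primary outcomes is handled.

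Cost: a change of wording, with no new data and no change to the sample size. The modelling is slightly heavier. The estimand becomes mean pain in all women rather than intensity among those with pain, and the plan should say so openly.

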## Results

After randomization we included 56 patients in the control group and 71 patients in the intervention group. The unequal randomization was caused by using the incorrect method, as we should have used a block randomization method. To correct the unequal distribution, we requested an amendment which was approved by the ethics committee. We wanted to include 200 women, resulting in 100 women in each arm. To reach this number of inclusions, we had to include an additional 29 women in the intervention group and an additional 44 women in the control group.

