### Patient recruitment, randomization and collection of data

Eligible patients are identified by the gynecologist or the resident in one of the two participating hospitals. Women eligible for the trial will be counseled by experienced research nurses or researchers. They will be informed about the aims, methods, reasonably anticipated benefits and potential hazards of the study. After a week patients will be asked if they want to participate and informed consent will be collected. By giving written informed consent, patients agree to participate and agree that their anonymous data may be used for publication.

Randomization will be performed by using sealed envelopes and will take place just before the end of the surgery.

The study is blinded for patients, but not for the gynecologist, as the gynecologist is the one who will leave normal saline intraperitoneal when necessary. Because this study is a multicenter trial, randomization will be stratified by hospital to get an equal distribution of patients between the two groups (control and intervention) per hospital. For randomization we used an Excel sheet that randomly assigned 200 patients (two lists of 100 patients, one for each hospital) to either the intervention or control group. Data handling will be done anonymously and the date code is only available to the local investigator. The baseline data and follow-up data collection at both hospitals is the responsibility of the two local investigators. Data will be stored in a sealed, anonymous files.

The dataset supporting the conclusions of this article will be available upon request. In accordance with the guidelines of the Dutch Federation of University Medical Centers (NFU), the data will be kept for 15 years.

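### Filling both arms to 100 after a chance 56:71 split ties treatment arm to recruitment stage, and the stated pooled tests do not account for stage

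*Protocol article*

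**What the plan says.** Under Patient recruitment, randomization and collection of data, the protocol article describes two Excel lists of 100, one per hospital, with sealed envelopes used shortly before surgery ends. The stated purpose is that "randomization will be stratified by hospital to get an equal distribution of patients between the two groups (control and intervention) per hospital".

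The Results section reports 56 control and 71 intervention women and explains: "The unequal randomization was caused by using the incorrect method, as we should have used a block randomization method". An amendment, approved by the ethics committee, then set a target of 100 women per arm. The consequence is given as: "we had to include an additional 29 women in the intervention group and an additional 44 women in the control group". The section does not say how these 73 women were assigned.

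Under Data analysis, the article states: "To compare the incidence of pain between the intervention and control groups, the Pearson’s Chi-squared statistic will be used". Pain scores are compared by t-test when normally distributed. Neither comparison names recruitment stage or hospital.

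**The concern.** Two things look wrong.

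First, the imbalance is diagnosed as a fault. Unblocked randomisation does not promise equal arms, and unequal arms alone do not bias a comparison.

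Second, the correction changes the allocation ratio part-way through. Women recruited after the amendment are more likely to be controls, so arm and calendar time become associated. If pain incidence, case mix, anaesthesia or questionnaire completion shifts between the two stages, part of that shift appears as a difference between arms. A pooled test cannot separate it from a treatment effect, whereas a comparison within stage can.

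**Working it through.** **Inputs.** From Results: stage 1 (before the amendment) has 71 intervention and 56 control women, 127 in total; stage 2 has 29 and 44, 73 in total; the target is 100 per arm. From Sample size: incidence 80% against 50%, power 85%, dropout 20%, Fisher's exact test, 63 per arm. From Data analysis: "Significance will be tested two sided with an α-level of 0.05".

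**1. The plan's own sample size.** Exact power of the two-sided Fisher test is 84.2% with 49 evaluable women per arm and 85.3% with 50. Allowing for dropout, 50 / 0.8 = 62.5, rounded up to 63 per arm, or 126. The stated figure is reproduced.

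**2. Was 56:71 a problem?**
- Exact two-sided binomial test of 71 out of 127 against 0.5: p = 0.21.
- Information relative to an equal split: 4 × 56 × 71 / 127² = 15,904 / 16,129 = 98.6%.
- Fisher power at 56 against 71 is 94.1%. After 20% dropout (56 × 0.8 = 44.8 and 71 × 0.8 = 56.8, so about 45 against 57) it is 87.7%, above the 85% target.

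The 127 women already exceeded the planned 126, and neither validity nor power required equal arms.

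**3. What the quota does to allocation.**
- Intervention share: 71/127 = 55.9% observed in stage 1 (nominal 50%) and 29/73 = 39.7% in stage 2.
- Share of each arm recruited in stage 1: 71/100 = 71% of intervention and 56/100 = 56% of control.
- Arm-by-stage odds ratio: (71 × 44) / (56 × 29) = 1.92.

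**4. Bias of the pooled risk difference.** Let p₁ and p₂ be the incidence in stages 1 and 2, with no treatment effect. The expected difference, intervention minus control, is (0.71 p₁ + 0.29 p₂) − (0.56 p₁ + 0.44 p₂) = 0.15 (p₁ − p₂). If incidence rises between stages, the intervention looks better than it is; if it falls, worse.

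**5. Type I error of the pooled chi-squared test.** The article gives no stage difference, so the values below are assumptions. Simulation used no treatment effect, 100 evaluable women per arm, the higher of the two stage incidences set at 80%, and 400,000 runs per scenario.

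| Assumed stage difference | Bias (points) | Two-sided type I error |
|---|---|---|
| 0 | 0 | 5.2% |
| 5 points (rising only) | 0.75 | 5.1% |
| 10 points | 1.5 | 5.5–5.6% |
| 20 points | 3.0 | 6.9–7.0% |
| 30 points | 4.5 | 8.9–9.5% |

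Ranges cover the two directions of change.

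**6. Cost of stratifying by stage.** Information within stages: 71 × 56 / 127 + 29 × 44 / 73 = 31.3 + 17.5 = 48.8. Pooled: 100 × 100 / 200 = 50.0. Ratio 97.6%, a loss of about 2.4%.

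**7. Had the 73 been allocated 1:1.** Expected totals are 71 + 36.5 = 107.5 and 56 + 36.5 = 92.5. Efficiency is 4 × 107.5 × 92.5 / 200² = 39,775 / 40,000 = 99.4%.

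**The case against.** The strongest reply is that the effect is partial and may be nil. With no stage difference the pooled test keeps its size, and up to about 10 points the inflation is negligible. Nothing in the article suggests any drift. The table also conditions on the split that occurred: averaged over possible first-stage splits under a fill-to-100 rule, type I error is 5.2%, 5.9% and 7.2% at 10, 20 and 30 points. Nor is all of the 15-point gap due to the quota. A 1:1 continuation would still leave 71/107.5 = 66.0% against 56/92.5 = 60.5%, a chance gap of 5.5 points, so the quota adds about 9.5 points. At a 20-point drift that is 0.095 × 20 = 1.9 points of added bias, small beside the planned 30-point effect. All of this stands and limits the size of the point. It does not remove it: the analysis will be run on the split that occurred, and adjustment is cheap.

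A separate analysis plan might already adjust for stage and hospital. If so, the analysis part of the fix is met; the test stated in the article does not do it.

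The Excel lists might have had fixed totals of 100 per arm, which would make 29:44 simply the remainder. A split of 56:71 would then be less likely (hypergeometric p about 0.04), and the article's own statement that blocking should have been used points the other way. Stage and arm would be associated in the data on that reading too.

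Three stronger readings are tempting, and the article does not support them:
- **That the pooled test is invalid because the ratio changed.** It is unprotected only if incidence differs between stages.
- **That the unblinded gynaecologist could predict late allocations.** The article does not say who holds or opens the envelopes, or whether anyone at the operating table knew the running tally.
- **That balance within hospital was abandoned.** Results gives overall totals only, and nothing withdraws the stratification by hospital.

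**Conclusion.** The point holds as a modest, conditional weakness with an inexpensive remedy. The imbalance that prompted the amendment was ordinary chance and did not need correcting. The quota links arm to recruitment stage (71% against 56% from stage 1), and the stated pooled tests leave that link uncontrolled. The expected bias is 0.15 times any stage difference in incidence, and type I error is about 5.5%, 7% and 9% at assumed differences of 10, 20 and 30 points, against 5% with none.

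These figures rest on the reported counts, 100 evaluable women per arm and dropout unrelated to stage. The drift sizes are assumptions. Whether the 73 were assigned at random within stage 2 is not stated; the protection from a stratified analysis depends on it.

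**What to change.** **Analysis, whether or not recruitment is finished.** Replace the pooled chi-squared test for incidence with a Cochran-Mantel-Haenszel test stratified by stage (before or after the amendment) and hospital. Adjust the pain-score comparison for the same two factors, for example in a linear model. Report incidence by arm within each stage. The cost is a sentence or two in the analysis section and about 2.4% of the information for stage. The cost for hospital cannot be computed because counts by hospital are not reported.

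**Reporting.** State how the 73 women after the amendment were assigned, and by hospital. Check the first 127 allocations against the two Excel lists, to confirm that 56:71 came from the lists themselves.

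**Allocation, only if women remain to be randomised.** The past tense in Results suggests there may be none. If there are, drop the arm quota, use concealed 1:1 blocked lists per hospital with varying block size, and accept the final split. If all 73 were allocated this way it would end near 92:108, at 99.4% efficiency, a loss of about 0.6%.
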